# Augmentative and alternative communication intervention for in-patient individuals with post-stroke aphasia: study protocol of a parallel-group, pragmatic randomized controlled trial

**DOI:** 10.1186/s13063-021-05799-0

**Published:** 2021-11-24

**Keywords:** Aphasia, Stroke, Augmentative and alternative communication, Speech-language therapy, Randomized controlled trial

## Abstract

**Background:**

People with post-stroke aphasia commonly receive speech-language therapy (SLT) when they are admitted to hospitals. Commonly, these patients reported communication difficulties in in-patient settings. Augmentative and alternative communication (AAC) has been reported as an effective treatment approach to improve communication effectiveness, language performance, decreasing depression, and improving quality of life for this population. However, little evidence has demonstrated the use of AAC intervention (AACT) in early recovery from people with post-stroke aphasia in in-patient rehabilitation settings for improving these patients’ communication effectiveness. The pilot randomized controlled trial (RCT) will explore the effectiveness and feasibility of including AACT in regular SLT for in-patient people with post-stroke aphasia.

**Method:**

This pilot RCT is a single-blind, randomized controlled trial with two parallel groups. Both groups receive a 1-h treatment session, including either both AACT and SLT or SLT only for ten consecutive days. We aim to include 22 in-patient participants with post-stroke aphasia in each group. Participants will be assessed at pre- and post-intervention and 2 weeks after intervention. The primary outcomes are the ability of communication measured by the communication of basic needs subtest in the Functional Assessment of Communication Skills for Adult (FACS) and the overall language performance measured by the Chinese Standard Aphasia Battery (ABC). The secondary outcomes include a 10-min conversation, the 10-item Hospital version of the Stroke Aphasic Depression Questionnaire (SADQH-10), the Stroke-Specific Quality of Life Scale (SS-QOL), and a patient and caregiver satisfaction questionnaire.

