### Objective

The present study focuses on the effectiveness of AACT combined with SLT for individuals with moderate to severe aphasia in in-patient rehabilitation settings. The primary aim is to evaluate whether people with aphasia who receive AACT with SLT have more functional communication and language performance improvement than those who received only SLT. The secondary aim is to evaluate the improvements in depression symptoms and quality of life after receiving AACT and SLT only.

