## Methods

### Study design and procedure

The study is a single-blind, pragmatic, pilot randomized controlled trial with two parallel groups. According to the PRECIS-2’s domains, the study is considered rather pragmatic because of the following characteristics [24]. People with moderate to severe aphasia usually receive speech-language therapy as part of usual care in in-patient settings in China. The participants of the study will be recruited from the study site from in-patient patients. When patients with aphasia are admitted in hospitals, they usually receive speech-language therapy daily for at least 2 weeks. The study design is based on the usual SLT schedule and extended the duration per treatment session for adding the AAC intervention in usual care. The primary outcome and analysis of the study is the improvement of functional communication which is also the essential outcome in the usual care.

Participants will participate in a 1-h treatment session/day for ten consecutive days. During each session, participants will receive 30 min of AACT in addition to 30 min of SLT (experimental group) or 60 min of SLT (control group). Participants in the AACT + SLT group will learn to use a paper-made communication board to express their needs. The communication board includes 45 pictures relating to basic needs, emotional expression, medical conditions, and daily activities. Participants’ regular rehabilitation interventions, such as physical and occupational therapies, remain the same during the experimental period.

The participants will be evaluated at pre-intervention (prior to randomization) for collecting the demographic and baseline data. The post-intervention evaluation will be completed after participants complete the 10-day training, which is 2 weeks after randomization. Last, a 2-week follow-up will be conducted after the post-intervention evaluation (see Fig. 1).

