### Measurement instruments

Table 2 provides an overview of the measurement instruments used in the study. The primary outcome measures are the scale of the Communication of Basic Needs (CBN) on the Functional Assessment of Communication Skills for Adults (FACS) [28, 29]. Communication recovery is an essential outcome when people with aphasia are in hospitals. Although professionals agree the outcome is important, there is no assessment tool in the Chinese language to evaluate the outcome. Therefore, the team translated the items of the CBN domain and its scoring scale to Chinese to measure the outcome of the AACT on communication effectiveness in a hospital setting.

**Table 2 Tab2:** Measurement instruments

Measurement instruments	Number of items	Score range	Measurement target
CBN subtest on the ASHA FACS	7	0–7	Functional communication skills for basic needs
ABC test	23	0–100	Language abilities, including speaking, listening, reading, and writing
10-min conversation	4	0–5	Communication efficiency in the in-patient setting
SADQH-10	10	0–3	Depression symptoms
SS-QOL	49	49–245	Stroke-specific health-related quality of life
Satisfaction questionnaire	11	1–5	Satisfaction intervention for communication improvement from both patients and their caregivers

The FACS measures functional communication skills of people with aphasia in four domains (social communication, communication of basic needs, reading/writing/number concepts, and daily planning) and in four qualitative dimensions (adequacy, appropriateness, promptness, and communication sharing). The 7-point scale measures the levels of assistance and prompting needed in each domain, and the 5-point scale measures the response in four dimensions. The inter-rater/intra-rater reliability for the CBN domain and the overall qualitative dimension are high. The concurrent validity between the Western Aphasia Battery and the Functional Independence Measure (FIM) is moderate [28].

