An informal test of a 10-min conversation is used to measure participants’ functional communication efficiency in the in-patient setting pre- and post-intervention. Conversation analysis is a common procedure in regular aphasia assessment [30]. The 10-min conversation is evaluated using the 5-point scale of the four qualitative dimensions (adequacy, appropriateness, promptness, and communication sharing) in the FACS. The results of the 5-point scale allow the team to evaluate changes of the quality of conversation pre- and post-intervention. The participants are asked to talk about their daily lives and their medical services with the SLP in the conversation. The conversation will be video recorded and analyzed by the SLP conducting the assessments.

The secondary measures include the Chinese Standard Aphasia Battery (ABC), a standard test to diagnose aphasia and determine the type of aphasia for the Chinese-speaking population and widely used in clinical practice and research in local sites, to measure participants’ overall language performance [25]. The Chinese version of the 10-item Hospital version of the Stroke Aphasic Depression Questionnaire (SADQH-10) with adequate content validity and the test-retest reliability (> 0.80) is used for evaluating depressive symptoms in people with aphasia [31, 32]. The Chinese version of the Stroke-Specific Quality of Life Scale (SS-QOL) with high stability and validity is used for evaluating the stroke-specific health-related quality of life [33, 34].

For qualitative evaluations, the first author designed a 5-point scale questionnaire to evaluate the satisfaction of the interventions for this trial. The questionnaire includes four items for both control and experimental groups, three items for both groups’ caregivers, and two extra items for the experimental group and the caregivers. The questions were reviewed by the research team to ensure the readability and appropriates. The participants and their caregivers are asked to choose from 1 (very dissatisfied) to 5 (very satisfied) to evaluate the satisfaction for materials (common cards and AAC paper board) and communication behavior with caregivers and medical professionals after the intervention.

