### Sample size

No large RCTs have been conducted in the field of aphasia AACT in in-patient rehabilitation settings. Previous AAC studies used interventions not applicable to the current protocol. Therefore, we are unable to calculate the prior accurate sample size. We will use the CBN score in the FACS to investigate the possible effect. We consider a minimum improvement of 1 point on the 7-point scale in FACS is clinically significant. Given an expected standard deviation of 1 based on prior norm references [28, 35], the trial must include a total of 44 participants. Each group needs 22 participants to detect this difference with a significance level of 5 and a power of 90. After considering a dropout rate of 20%, the study aims to recruit 56 participants in total. We anticipate that this pilot study will provide information for more accurate sample size calculation in the future.

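### The abstract makes the ABC language battery a primary outcome, the methods make it secondary, and the sample size covers CBN alone

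*Protocol article*

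**What the plan says.** All references are to the protocol article.

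**ABC as primary.** In the Method part of the Abstract, the sentence on primary outcomes names the CBN subtest and continues "and the overall language performance measured by the Chinese Standard Aphasia Battery (ABC"). The next sentence opens "The secondary outcomes include a 10-min conversation, the 10-item Hospital version of the Stroke Aphasic Depression Questionnaire (SADQH-10") and goes on to quality of life and satisfaction; ABC is not in it. So the abstract puts ABC in the primary set and keeps it out of the secondary set.

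**Language in the primary aim.** Under Objective, the primary aim is to see whether patients given the combined treatment "have more functional communication and language performance improvement than those who received only SLT". No instrument is named there. The Discussion likewise states the primary objective in terms of both communication and language.

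**CBN as the only primary.** Study design and procedure says "The primary outcome and analysis of the study is the improvement of functional communication". Measurement instruments says "The primary outcome measures are the scale of the Communication of Basic Needs (CBN") and names no other primary measure. Further on, the same section says "The secondary measures include the Chinese Standard Aphasia Battery (ABC"), to measure overall language performance.

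**Sample size.** This section says "We will use the CBN score in the FACS to investigate the possible effect" and "We consider a minimum improvement of 1 point on the 7-point scale in FACS is clinically significant". With an SD of 1, a 5% level and 90% power it arrives at 22 per group, 44 in total, and 56 after 20% dropout. ABC plays no part in it.

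**The concern.** ABC cannot be both a primary and a secondary outcome. The article states the primary outcome set more than once and the statements differ. This is therefore not a detail left to an unseen analysis plan, and since Trial status describes this as the first version, it is not a leftover from an amendment either.

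The two instruments measure different things: CBN rates functional communication of basic needs, and ABC rates language ability across speaking, listening, reading and writing. The experimental arm gives up half of its hour of conventional language therapy for communication-board training, so a result that favours the combination on one instrument and not on the other is plausible. In that case the answer to whether the trial met its primary aim would depend on which section is followed, and that choice could be made after the results are known.

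If ABC really were primary, a success rule would be needed (either outcome or both), and the sample size would have to reflect it. It reflects one test only.

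**Working it through.** **Inputs.** From Sample size: difference 1 point, SD 1, level 5%, power 90%, 22 per group, 20% dropout. From Randomization and blinding: 1:1 allocation. Sidedness is not stated. The correlation between the CBN and ABC tests and the effect on ABC are not given either; both are assumptions below.

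**1. Reproduce the stated sample size.** Normal formula for two means: n per group = 2(z₁₋α/₂ + z₁₋β)² SD²/δ².
- Two-sided 5%: 2(1.960 + 1.282)² = 21.0, rounded up to 22. Noncentral t power at 22 per group (42 df) is 90.0%.
- One-sided 5%: 2(1.645 + 1.282)² = 17.1, rounded up to 18, which does not match.
- Dropout: 22/0.8 = 27.5, rounded up to 28 per group, or 56 in total.

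The stated 22, 44 and 56 therefore follow from one two-sided 5% test on CBN. Two-sided testing is inferred from this match.

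**2. If both were primary and either could succeed, each at 5%.** Independent outcomes: 1 − (1 − 0.05)² = 0.0975. With correlated tests, the family-wise error is 1 − P(|Z₁| < 1.96 and |Z₂| < 1.96) from the bivariate normal:

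| Assumed correlation | Family-wise error |
|---|---|
| 0 | 9.75% |
| 0.5 | 9.1% |
| 0.7 | 8.3% |
| 0.8 | 7.8% |
| 0.9 | 7.0% |

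**3. If the level were split, 2.5% for each.** Noncentral t power on CBN at 22 per group falls from 90.0% to 83.5%. To restore 90%, the normal formula gives 2(2.241 + 1.282)² = 24.8, so 25 per group; the noncentral t gives 27.

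**4. If both had to succeed, each at 5%.** There is no inflation of the error rate, but power falls. Assuming a 1 SD effect on ABC as well, independent outcomes give 0.8997² = 0.809, about 81%. Simulating pairs of t tests at 22 per group gives about 85% at a correlation of 0.7. The documents give no basis for a 1 SD effect on ABC, so this range is illustrative.

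**5. If CBN is the sole primary.** One test at 5%, 90.0% power, 22 per group: the plan as sized.

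**The case against.** The best defence is that the body of the article largely settles the matter. Study design and procedure, Measurement instruments and Sample size all point to CBN as the one primary outcome, and only the abstract calls ABC primary outright. On this view the abstract was simply not matched to the methods. That is probably how the conflict arose, and it supports the proposed fix. It does not remove the conflict, because the abstract and the primary aim could still be cited for a primary claim on ABC.

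A second defence is that this is a pilot meant to explore effectiveness and feasibility and to inform a later sample size, so strict error control matters less. That lowers the stakes. Yet the article sets a 5% level and 90% power and states an effectiveness aim, so it does commit to a test whose outcome should be unambiguous.

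Three stronger readings are tempting and are not supported:

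- A reader might infer that the trial will declare success on either outcome, so that its error rate is nearly 10%. No section states such a rule. The error rates above show what would follow from it; they do not describe the plan.
- A reader might take the statement in Data analysis that the primary analysis is done without adjustment as a refusal to control multiplicity. It may equally well mean no adjustment for covariates, and it carries no weight here.
- A reader might say that Objective itself designates ABC as primary. It names no instrument. The link to ABC is a fair inference, since the abstract and Measurement instruments both use ABC for overall language performance, but the passage only supports the point.

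The absence of a testing hierarchy is not a fault in itself, since that is commonly left to an analysis plan.

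**Conclusion.** The point stands as an internal contradiction over which outcome decides the trial. The abstract makes ABC primary and the methods make it secondary; the primary aim leans towards the abstract, while the sample size follows the methods and is correct for CBN alone.

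The size of the problem depends on a success rule the article does not give. Across the possible rules, either the 5% level is exceeded (9.75% at most, less as the assumed correlation rises) or power falls short of 90% (83.5% on CBN with an equal split; about 81% to 85% if both must succeed, assuming 1 SD on ABC). Only the single-primary reading delivers the stated 5% and 90%. All these figures assume two-sided tests and 22 analysed per arm. The contradiction itself depends on none of them.

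**What to change.** Name CBN at the post-intervention assessment as the single primary outcome wherever the primary outcome or aim is stated. In the Abstract, move ABC from the primary to the secondary list. In Objective, reword the primary aim so that it concerns functional communication, and place language performance with the secondary aims; bring the statement of the primary objective in the Discussion into line. Study design and procedure, Measurement instruments and Sample size already fit and need no change on this point.

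Optionally, add one line saying that ABC will be tested at 5% only if CBN is significant. This would give ABC a protected place but is not needed to remove the contradiction.

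The cost is wording. The sample size stays at 22 per arm, with 56 recruited, and no assessments are added. The one real loss is that ABC can no longer support a primary claim by itself. The article's Ethics approval section requires a formal amendment for changes to study objectives that may affect the conduct of the study or benefit to patients, so rewording the aim may have to go through that route. Trial status reports 14 participants randomized out of the planned 56, so the change can still be made before most of the data exist.

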**Discussion:**

This pilot RCT will contribute to new scientific evidence to the field of aphasia rehabilitation in early recovery during the in-patient period. The paper describes the trial, which will explore the effect of combining AACT and SLT and SLT only, our choice of primary and secondary outcome measures, and proposed analyses. The study results will provide information for implementing AACT in the regular in-patient SLT of future RCTs.

**Trial registration:**

Chinese Clinical Trial Registry database (ChiCTR) ChiCTR2000028870. Registered on 5 January 2020

**Supplementary Information:**

The online version contains supplementary material available at 10.1186/s13063-021-05799-0.

## Background

Stroke is a leading cause of disability worldwide [1]. Nearly one-third of patients with stroke have post-stroke aphasia [2–4], which is defined as an impairment of the complex process of interpreting and formulating language symbols affecting auditory comprehension, reading, and oral-expressive language and writing [2, 4]. People with aphasia commonly experience different levels of expressive language impairments, ranging from occasional word-finding difficulties to severe verbal communication difficulties [4]. These language and communication difficulties often affect patients’ emotions and quality of life [5–8].

When people with aphasia are admitted to hospitals after stroke, they usually receive speech-language therapy (SLT) to improve their language and communication abilities [4, 9, 10]. However, they often reported difficulties in expressing their daily-life and medical needs because of aphasia. Meanwhile, caregivers and healthcare professionals also reported difficulties when communicating with people with aphasia [11]. Therefore, besides SLT, augmentative and alternative communication (AAC) becomes a solution for the issue. AAC is a rehabilitation approach that helps people with aphasia communicate with others [12–14]. People with aphasia can use aided AAC systems (e.g., communication books or high-tech computer devices) to communicate basic needs, deliver information, maintain social closeness, and use social etiquette [12, 15].

Historically, AAC intervention (AACT) was primarily used to support people with aphasia’s communication needs as a compensatory strategy but was not used to restore their language abilities [14–18]. Currently, few studies reported that AACT could facilitate language recovery. Several AAC treatment studies have documented people with aphasia’s improvements in overall language performance and spoken discourses to unfamiliar listeners [19–21]. Moreover, people with aphasia also showed the ability to use the letters on an AAC device or a communication board to facilitate spoken language during communication breakdowns [20, 22]. However, there is still a lack of evidence of the effectiveness of AAC practices in in-patient rehabilitation settings. Thus, an understanding of AAC practices and supports related to serving individuals with post-stroke aphasia in in-patient rehabilitation settings is essential to develop evidentiary AAC intervention in the specific setting.

It is also important to note that there is limited evidence of AACT for Chinese-speaking people with aphasia. People with aphasia in in-patient rehabilitation settings in China are mainly in acute rehabilitation or subacute facilities. Their communication demands include expressing basic and medical needs (e.g., asking a nurse to call a family member). They need to share information and feelings with their family members and interact with medical professionals about needs and concerns with regard to their healthcare. Evidence indicated that this population could learn to use yes/no cards and communication boards with pictures and words for different communication needs [12]. While the previous studies supported the concept of using AAC in hospital settings [8, 11], there is still no evidence to support this approach in Chinese-speaking people with aphasia. Therefore, an AACT RCT study is needed to investigate the feasibility of the AACT and build up the foundation of research evidence in Chinese communities.

In addition, previous studies have reported that people with aphasia and their families often reject to adopt AAC strategies with the fear that AAC may interfere with or impede the restoration of their natural language system [14, 19, 23]. Similar concerns are commonly raised in the clinical settings in China. However, studies have shown that AACT may simultaneously strengthen communication by reducing the pressure to retrieve target concepts using impaired language functions [20]. Since the present study aims to introduce a new approach (AACT) in an in-patient rehabilitation setting, considering the potential concern of people with aphasia and their families becomes essential. Therefore, instead of comparing AACT and SLT exclusively, the present study aims to compare AACT’s effect along with regular SLT to SLT only in individuals with post-stroke moderate to severe aphasia in an in-patient rehabilitation program.

### Objective

The present study focuses on the effectiveness of AACT combined with SLT for individuals with moderate to severe aphasia in in-patient rehabilitation settings. The primary aim is to evaluate whether people with aphasia who receive AACT with SLT have more functional communication and language performance improvement than those who received only SLT. The secondary aim is to evaluate the improvements in depression symptoms and quality of life after receiving AACT and SLT only.

